## Discussion

3

Although attention is one of the six central cognitive domains and a fundamental function required for many other cognitive processes (Falkai et al., 2018), and studies on sustained attention across different age groups show significant differences in performance and neural dynamics in older adults (McAvinue et al., 2012; Langner and Eickhoff, 2013; Fortenbaugh et al., 2015), research on this topic in the neurogeriatric field is rare. The study presented here will investigate whether EEG has the potential to provide objective and quantitative surrogate markers of sustained attention in neurogeriatric patients. In particular, we aim to determine possible EEG changes during active task performance and during inactive (“recovery”) phases. These findings may help to elucidate pathomechanisms underlying sustained attention deficits, with potential therapeutic implications.

The strength of our proposed study lies in investigating a typical neurogeriatric population at a university hospital, covering a wide range of neurological conditions and cognitive abilities. Furthermore, the protocol employs a comprehensive multimodal assessment strategy. Sustained attention will be examined using three complementary paradigms, the cued Go-NoGo task, the PVT, and the AKT, thereby capturing sustained attention across computerized reaction-time paradigms as well as a conventional paper–pencil format commonly used in geriatric settings. Within these tasks, sustained attention will be quantified not only by mean reaction times but also through omission and commission errors, and intra-individual reaction time variability, reflecting complementary aspects of vigilance performance.

On the electrophysiological level, the combination of ERP measures (N200, P300) and spectral power analyses allows for a differentiated characterization of neural dynamics associated with sustained attention (Polich, 2007; Clayton et al., 2015; Liu et al., 2020). Given that EEG recordings in older and multimorbid patients are often associated with increased movement-related and physiological artifacts (Urigüen and Garcia-Zapirain, 2015; Geraedts et al., 2018), particular attention will be paid to data quality and preprocessing procedures. Artifact correction using ICA in combination with automated component classification (ICLabel) will be applied, alongside visual inspection, to ensure careful handling of artifact-prone recordings. The integration of behavioral, electrophysiological, clinical, and self-reported measures strengthens construct validity and enables the examination of sustained attention within a clinically meaningful and ecologically valid framework. Important covariates that are known to impact treatment success and quality of life will also be considered. Moreover, in a subgroup, we will examine potential changes in sustained attention performance over 2–3 weeks of complex geriatric treatment.

From an analytical perspective, the study is designed to go beyond descriptive comparisons and to examine associations between behavioral and electrophysiological markers using correlational and multivariate approaches. We expect sustained attention performance indices (e.g., reaction time variability) to correlate with ERP parameters, particularly P300 amplitude and latency, as well as with frontal theta and global alpha power. Multiple regression analyses will allow us to determine whether EEG markers explain variance in sustained attention performance beyond global cognitive status (MoCA), age, and affective symptom burden. Exploratory moderation analyses using regression models with interaction terms will examine whether fatigue, depressive symptoms, or sleep quality influence the relationship between behavioral performance and neural markers. This analytical framework allows differentiation between electrophysiological parameters that reflect sustained attention specifically and those that may represent broader cognitive or affective influences.

In conclusion, this study aims to provide a structured and multimodal characterization of sustained attention in neurogeriatric patients. More specifically, it aims to evaluate the potential of EEG-derived parameters as clinically meaningful surrogate markers for the detection and monitoring of sustained attention deficits in this vulnerable cohort.

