**Methods/design:**

The study “Studying Neurocognitive Systems for Sustained Attention in Neurogeriatrics Patients” (SENSE-AGE) is a prospective, explorative, observational study and will include 120 geriatric participants. At admission, participants will perform a Go-NoGo task, a Psychomotor Vigilance Task (PVT) and resting-state condition during EEG recording, using a 32-channel system. Task-based event-related potentials (ERPs) and frequency-band power will be extracted. Neuropsychological tests characterize global and domain-specific cognition and will examine associations between sustained attention, broader cognitive performance, and EEG parameters. Questionnaires will assess fatigue, sleep, health-related quality of life, and subjective cognition. A subgroup of 50 participants will be re-evaluated at the end of the inpatient stay, after 2–3 weeks of standardized geriatric complex treatment. The main hypotheses of the study are: sustained attention (i) correlates with ERP amplitude and latency; (ii) correlates with EEG power; (iii) improves after an inpatient multiprofessional complex treatment at both the task-performance and neurophysiological level.

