### Participants

2.2

Participants will be neurogeriatric, defined as > 70 years with a primary neurological disease [participants between 50 and 69 years of age can also be included if they have at least two chronic diseases (> 6 months)] [ Sieber, 2007; Maetzler et al., 2016; Johnston et al., 2019). Other inclusion criteria are the ability to consent to the study and, if applicable, the consent of the legal representative, as well as at least 5 points on the Montreal Cognitive Assessment (MoCA, (Nasreddine et al., 2005)].

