#### Cognition

2.4.2

Global cognitive functioning will be assessed using the MoCA, a screening instrument covering multiple cognitive domains. The test yields a total score ranging from 0 to 30, with higher scores indicating better cognitive performance; a score below 26 is commonly used as a cut-off for cognitive impairment. It has good internal consistency (Cronbach’s alpha = 0.83) and a high sensitivity in the detection of MCI (90%) and AD (100%) (Nasreddine et al., 2005).

Processing speed and executive functioning will be evaluated using the Trail Making Test (TMT). TMT Part A primarily assesses visual scanning and psychomotor processing speed, whereas Part B additionally requires task switching and cognitive flexibility, reflecting divided attention and executive control. Performance is measured as completion time in seconds, with longer times indicating poorer performance. The TMT shows good construct validity and sensitivity to executive dysfunction in clinical populations (Sánchez-Cubillo et al., 2009). These instruments are included to describe global cognitive status and executive functioning and will be treated as covariates in regression models. They are not considered direct measures of sustained attention.

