### Limitations due to missing control group

3.1

The absence of a control group precludes any conclusion regarding the extent of sustained attention deficits due to mere age-related changes in sustained attention. In addition, several practical challenges may arise when implementing EEG protocols in a neurogeriatric inpatient population. Increased movement, tremor, reduced tolerance for prolonged testing, and medication effects may introduce variability into electrophysiological measures. Fatigue-related fluctuations during the computerized sustained attention tasks may also differentially affect early vs. late task phases. The clinical heterogeneity of the cohort, while increasing ecological validity, may lead to increased variance and reduced statistical power for specific subgroup effects. Moreover, the observational design limits the interpretability of results concerning potential causal inference between sustained attention, EEG parameters, and psychosocial variables.

For the subsample of participants who will be measured twice, the absence of a control group precludes a definitive conclusion regarding the extent to which any observed changes over the study period can be attributed to the complex geriatric treatment, as opposed to other potential influences, such as an extended stay in hospital or care facility in general. Additionally, even considering the generally good retest reliabilities of resting-state and task-based EEG measures, it will not be possible to causally attribute the observed changes in ERPs or power to the treatment of the participants (Näpflin et al., 2008; Vázquez-Marrufo et al., 2020; Popov et al., 2023).

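### An EEG association that survives adjustment for the observed MoCA score does not by itself show that the marker is specific to sustained attention

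*Protocol article*

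**What the plan says.** The Discussion (section 3) says that multiple regression will determine "whether EEG markers explain variance in sustained attention performance beyond global cognitive status (MoCA), age, and affective symptom burden". After mentioning moderation models it concludes: "This analytical framework allows differentiation between electrophysiological parameters that reflect sustained attention specifically and those that may represent broader cognitive or affective influences".

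Section 2.4.2 (Cognition) says of the MoCA: "It has good internal consistency (Cronbach’s alpha = 0.83", citing the instrument's validation paper. The same section states that the MoCA and the Trail Making Test "will be treated as covariates in regression models". It gives no reliability for the TMT.

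The abstract says the study "will include 120 geriatric participants". Section 2.2 admits patients with "at least 5 points on the Montreal Cognitive Assessment", on a scale that runs to 30.

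Section 2.5.1 sets up the reverse model (EEG component as outcome, task performance as predictor) and controls for cognitive status. The nearest stated limitation, in section 3.1, is that "the observational design limits the interpretability of results concerning potential causal inference between sustained attention, EEG parameters, and psychosocial variables". Measurement error in the covariates is not mentioned anywhere.

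**The concern.** The Discussion draws a conclusion about a construct (specific to sustained attention, as against broader cognition) from adjustment for a score. When the score measures the construct with error, adjustment removes only part of the shared influence. What is left is picked up by any other variable that also tracks general cognition, including an EEG marker with no specific link to attention. An association beyond the observed MoCA is then not the same as an association beyond global cognition.

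The cohort makes this more than a formality. Admitting MoCA scores from 5 upward gives a wide spread of cognitive ability, which could plausibly drive both task performance and EEG. The problem also does not fade with sample size, because it is a bias: more patients make the residual association easier to detect. At stake is which EEG parameters are put forward as attention-specific, and the study's aim is to evaluate candidate surrogate markers.

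**Working it through.** The article gives no power or error-rate figure for this regression, so there is nothing to reproduce. The check asks how often a marker of general cognition only would be significant after the planned adjustment.

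**Inputs from the article:** n = 120; MoCA alpha 0.83; covariates MoCA, age and affective burden (Discussion); TMT as a further covariate (section 2.4.2).

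**Assumptions, not in the article:** two-sided 5% test; one general factor G; EEG loads a and performance loads b on G, and they share nothing else; a = 0.3-0.6 and b = 0.5-0.7; age and affect unrelated to G; TMT-A and TMT-B each share 50% of variance with G.

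**Step 1, residual association.** With covariate reliability ρ, the partial correlation given the observed score is

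r = ab(1 − ρ) / √[(1 − ρa²)(1 − ρb²)],

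which is above zero whenever ρ < 1.

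**Step 2, effect of TMT.** Several proxies of G act like one with ρ* = S/(1 + S), where S is the sum of ρ/(1 − ρ). MoCA alone: 0.83/0.17 = 4.88. Each TMT part adds 0.5/0.5 = 1. So S = 6.88 and ρ* = 6.88/7.88 = 0.873.

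**Step 3, chance of significance.** m = atanh(r) × √(n − k − 3), where k is the number of covariates. MoCA, age and affect give k = 3 and √114 = 10.68. Adding two TMT scores gives k = 5 and √112 = 10.58. The rate is Φ(m − 1.96) + Φ(−m − 1.96).

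**Example, a = 0.6, b = 0.7, MoCA alone.** r = 0.42 × 0.17 / √(0.7012 × 0.5933) = 0.0714/0.645 = 0.111. Then m = 0.1112 × 10.68 = 1.187, and the rate is Φ(−0.773) + Φ(−3.147) = 22.1%.

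| a / b | r, MoCA alone | rate | r, MoCA + TMT-A + TMT-B | rate |
|---|---|---|---|---|
| 0.3 / 0.5 | 0.030 | 6.2% | 0.022 | 5.6% |
| 0.4 / 0.6 | 0.052 | 8.7% | 0.040 | 7.0% |
| 0.5 / 0.6 | 0.068 | 11.3% | 0.052 | 8.5% |
| 0.5 / 0.7 | 0.087 | 15.3% | 0.066 | 10.8% |
| 0.6 / 0.7 | 0.111 | 22.1% | 0.085 | 14.7% |

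Simulation of the MoCA-only column gave 6.5%, 9%, 12%, 17% and 22%. With an error-free covariate, simulation (equal loadings of 0.5 to 0.8) gave 5.1-5.5%, so the excess comes from the measurement error.

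**Step 4, other reliabilities, same five scenarios.**

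| MoCA reliability | MoCA alone | with TMT-A and TMT-B |
|---|---|---|
| 0.75 | 7.5-38% | 6-21% |
| 0.83 | 6.2-22.1% | 5.6-14.7% |
| 0.90 | 5.4-11.3% | 5.3-9.4% |
| 0.95 | 5.1-6.7% | 5.1-6.4% |

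**Step 5, sample size.** At a = b = 0.5, reliability 0.83 and MoCA alone, the rate is 8.8% at n = 120 and would be 22.2% at n = 500.

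**Step 6, is a correction at a fixed 0.83 safe?** The uncorrected residual covariance is ab(1 − ρ). After correction at an assumed 0.83 it is ab(1 − ρ/0.83), which turns negative once ρ exceeds 0.83. The two are equal in size when ρ/0.83 − 1 = 1 − ρ, that is at ρ = 2/(1 + 1/0.83) = 0.907. Above that, the fixed correction is further from zero than no correction. This argues for a range of reliabilities.

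**The case against.** The strongest reply is that any regression adjusting for a test score is open to this objection, that the study is declared explorative, and that the target is one Discussion sentence in a condensed article. Exploratory status does mean that no confirmatory error rate is at stake. It does not support a flat statement that the framework can separate the two kinds of marker. That statement is in the article itself and is not a detail left to an analysis plan.

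Several further objections stand and limit the point:

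- Section 2.4.2 makes TMT a covariate too. It lowers the excess without removing it, so the MoCA-only figures overstate the leak if TMT is entered.
- The loadings are assumptions. At 0.3 for both, the rate is 5.4%, which is negligible.
- Alpha 0.83 is not this cohort's reliability. The wide MoCA range could raise it, and at 0.90 the excess is small to moderate.
- The MoCA spans several domains and the Introduction treats attention as a core domain. Adjusting for MoCA may also remove genuine attention variance, an opposing bias that the one-factor model cannot show.
- Other planned evidence bears on what a marker reflects: convergence across three attention tasks, and comparison with perceived difficulties. It does not remove the measurement error. The reverse model in section 2.5.1 is no independent check, because with one marker, one index and the same covariates it tests the same partial association.

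A reader might infer a stronger criticism: that the plan states a formal null of no specificity, sorts every marker by significance, and labels the non-significant ones as broader influences. The article states no such null or rule. It says only that differentiation is possible and that some parameters may represent broader influences. A true partial correlation of 0.20 would be missed in about 42% of studies of this size, and one of 0.25 in about 23%. That is ordinary power, not a consequence of measurement error in MoCA. It is only a reason not to read non-significance as evidence of absence.

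**Conclusion.** The point holds as a limit on interpretation. A significant EEG coefficient after adjustment for observed MoCA, age and affective burden does not by itself establish specificity to sustained attention, and the Discussion sentence claims more than the model can deliver. That the residual association is non-zero follows from imperfect reliability in the one-factor setting and needs no particular loading.

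Its size does depend on assumptions. At reliability 0.83, n = 120 and the stated loadings, the false-specific rate is about 6-22% with MoCA alone and about 6-15% with both TMT parts. At reliability 0.90 it is about 5-11% and 5-9%. The inflation is therefore modest in many plausible settings and becomes serious only when both EEG and performance depend strongly on general cognition. It should be corrected, but it does not invalidate the planned associations themselves.

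**What to change.** - Keep the planned regression and enter both MoCA and TMT as covariates, as section 2.4.2 provides.
- Add a sensitivity analysis that corrects MoCA for measurement error, by errors-in-variables or a single-indicator latent variable, over reliabilities of about 0.75 to 0.95. Do not rest the claim on one value fixed at 0.83.
- Call a marker attention-specific only if its coefficient and 95% CI hold across that range. Report a non-significant adjusted coefficient as inconclusive.
- Reword the Discussion sentence so that it claims *association beyond measured MoCA and TMT*.
- Add residual confounding from covariate measurement error to section 3.1.

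The cost is a little more analysis, wider intervals and fewer markers labelled specific. In one simulated case with a true specific link, correction at 0.83 lowered detection from 97% to 83%. No new data are needed.

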### Limitations due to missing control group

3.1

The absence of a control group precludes any conclusion regarding the extent of sustained attention deficits due to mere age-related changes in sustained attention. In addition, several practical challenges may arise when implementing EEG protocols in a neurogeriatric inpatient population. Increased movement, tremor, reduced tolerance for prolonged testing, and medication effects may introduce variability into electrophysiological measures. Fatigue-related fluctuations during the computerized sustained attention tasks may also differentially affect early vs. late task phases. The clinical heterogeneity of the cohort, while increasing ecological validity, may lead to increased variance and reduced statistical power for specific subgroup effects. Moreover, the observational design limits the interpretability of results concerning potential causal inference between sustained attention, EEG parameters, and psychosocial variables.

For the subsample of participants who will be measured twice, the absence of a control group precludes a definitive conclusion regarding the extent to which any observed changes over the study period can be attributed to the complex geriatric treatment, as opposed to other potential influences, such as an extended stay in hospital or care facility in general. Additionally, even considering the generally good retest reliabilities of resting-state and task-based EEG measures, it will not be possible to causally attribute the observed changes in ERPs or power to the treatment of the participants (Näpflin et al., 2008; Vázquez-Marrufo et al., 2020; Popov et al., 2023).

## Conclusion and outlook

4

Taken together, this protocol presents a multimodal framework to investigate sustained attention in neurogeriatric patients by integrating behavioral, electrophysiological, and psychosocial measures. By examining associations between EEG-derived parameters and behavioral sustained attention performance, the study aims to clarify the neural correlates of sustained attention in a clinically relevant cohort. The findings may inform future longitudinal and interventional research targeting attention deficits in neurogeriatric care.
